# Effects of a Brazilian cardioprotective diet and nuts on cardiometabolic parameters after myocardial infarction: study protocol for a randomized controlled clinical trial

**DOI:** 10.1186/s13063-021-05494-0

**Published:** 2021-09-01

**Keywords:** Myocardial infarction, Nuts, Atherosclerosis, Secondary prevention, Diet, Healthy, Arachis, Bertholletia, Anacardium

## Abstract

**Background:**

Nut consumption has been related to improvements on cardiometabolic parameters and reduction in the severity of atherosclerosis mainly in primary cardiovascular prevention. The objective of this trial is to evaluate the effects of the Brazilian Cardioprotective Diet (***DI****eta*
***CA****rdioprotetora*
***Br****asileira*, DICA Br) based on consumption of inexpensive locally accessible foods supplemented or not with mixed nuts on cardiometabolic features in patients with previous myocardial infarction (MI).

**Methods:**

DICA-NUTS study is a national, multicenter, randomized 16-week follow-up clinical trial. Patients over 40 years old with diagnosis of previous MI in the last 2 to 6 months will be recruited (*n* = 388). A standardized questionnaire will be applied to data collection and blood samples will be obtained. Patients will be allocated in two groups: Group 1: DICA Br supplemented with 30 g/day of mixed nuts (10 g of peanuts, 10 g of cashew, 10 g of Brazil nuts); and Group 2: only DICA Br. The primary outcome will consist of LDL cholesterol means (in mg/dL) after 16 weeks of intervention. Secondary outcomes will consist of other markers of lipid profile, glycemic profile, and anthropometric data.

**Discussion:**

It is expected that DICA Br supplemented with mixed nuts have superior beneficial effects on cardiometabolic parameters in patients after a MI, when compared to DICA Br.

**Trial registration:**

ClinicalTrials.gov Identifier NCT03728127. First register: November 1, 2018; Last update: June 16, 2021. World Health Organization Universal Trial Number (WHO-UTN): U1111-1259-8105.

**Supplementary Information:**

The online version contains supplementary material available at 10.1186/s13063-021-05494-0.

## Administrative information

The order of the items has been modified to group similar items (see http://www.equator-network.org/reporting-guidelines/spirit-2013-statement-defining-standard-protocol-items-for-clinical-trials/).

**Table Taba:** 

Title {1}	Effects of a Brazilian Cardioprotective Diet and Nuts on Cardiometabolic Parameters after Myocardial Infarction: study protocol for a randomized controlled clinical trial.
Trial registration {2a and 2b}.	Brazilian Cardioprotective Diet and Nuts in Post-acute Myocardial Infarction (DICA-NUTS). Trial Registration: ClinicalTrials.gov Identifier NCT03728127. First register: November 1, 2018; Last update: June 16, 2021. World Health Organization Universal Trial Number (WHO-UTN): U1111-1259-8105
Protocol version {3}	Fourth version (approved by HCor-REC in 05/15/2019).
Funding {4}	Hospital do Coração (HCor); *Programa de Apoio ao Desenvolvimento Institucional do Sistema Único de Saúde* (PROADI-SUS); Brazilian Ministry of Health.

Role of sponsor {5c}	The sponsor had approved the final version of this manuscript and the decision to submit the report for publication.

## Introduction

### Background and rationale {6a}

Ischemic heart disease (IHD) is the most common cause of mortality worldwide [1]. Myocardial infarction (MI) is the principal responsible for deaths from IHD [2], and it is expected that, within 1 year after a MI at ≥ 45 years of age, 18% of men and 23% of women will die in developed countries [1].

In addition to physiological features including high blood pressure, high blood cholesterol, and high blood glucose, dietary factors have been associated with a substantial number of deaths from heart diseases [3], and improving global eating patterns might prevent premature mortality from IHD [4]. Thus, foods and dietary patterns related to primary and secondary cardiovascular prevention are of great scientific interest.

Mediterranean diet is related to lower cardiovascular mortality [5], and the effects of its adaptations/variations on cardiometabolic features in post-MI individuals have been described [6–8]. However, despite regional adaptations, many Mediterranean diet foods are not widely available, may be expensive, or are not part of local eating habits in Brazil [9]. In this scenario, the Brazilian Cardioprotective Diet (***DI****eta*
***CA****rdioprotetora*
***Br****asileira*, DICA Br) was developed, based on a feasible dietary prescription guided by nutritional recommendations and on a ludic strategy for improving dietary compliance in adults with any atherosclerotic cardiovascular disease. In general, the DICA Br features nutritional recommendations that are feasible for the Brazilian population. Accordingly, the diet composition allows for the easy access and full use of foods, in addition to the prioritization of regional foods that are culturally accepted by the patients (rice, bean, soy oil, and Brazilian fruits and vegetables) [10–12].

Nuts and peanuts are rich in vegetal proteins, unsaturated fatty acids, and other bioactive components, such as dietary fibers, minerals, vitamins, phytosterols, and phenolic compounds [13, 14]. Furthermore, nut consumption has been related to lower IHD incidence [15]. Systematic reviews and metanalyses from randomized trials have shown the effects of different nuts and peanut intake on cardiometabolic features in primary cardiovascular prevention [16, 17] but few clinical trials have been conducted in individuals with previous IHD [8, 18–21]. In addition, these studies show discrepancies in the results, possibly due to different sample sizes and differences in the dietary pattern adopted for both intervention and control groups, intervention duration, design, population, and type of nuts evaluated [8, 16–19].

Guidelines for secondary cardiovascular prevention have suggested that 30 g/day of nut intake may be related to benefits for individuals already affected by a MI [22, 23]. However, references that support this recommendation were cited from observational or experimental studies conducted in primary prevention [24, 25]. DICA Br was effective in improving the diet quality of individuals in secondary cardiovascular prevention but did not change cardiometabolic risk factors [12]. Moreover, the intake of nuts is not genuinely stimulated in DICA Br, which does not emphasize the consumption of specific foods individually.

Considering that DICA Br is a regional and feasible dietary pattern, but it was assessed in a heterogeneous population, and considering also that benefits of consuming different nuts are not well established in the secondary cardiovascular prevention setting (mainly in post-MI), we designed a randomized clinical trial to evaluate and compare the effects of DICA Br supplemented or not with mixed nuts widely available in Brazil on cardiometabolic parameters in individuals with previous MI.

### Objectives {7}

Our primary objective is to evaluate the effect of two dietary approaches (DICA Br supplemented or not with 30 g/day of mixed nuts) on low-density lipoprotein cholesterol (LDL-c) levels in patients with previous MI after 16 weeks of follow-up.

The secondary objective is to evaluate the effects of both dietary approaches on other lipid profile variables, glycemic, and anthropometric features after 16 weeks of follow-up.

### Trial design {8}

The DICA-NUTS study is a national, multi-centered, randomized, open-label, parallel-group (1:1 allocation ratio), and superiority 16-week clinical trial with blinded outcome assessment.

## Methods: participants, interventions, and outcomes

### Study setting {9}

The study will be conducted in investigation sites across 4 Brazilian regions (Northeast, Southeast, South, and Midwest regions). HCor Research Institute (IP-HCor, São Paulo, Brazil) is responsible for the protocol and coordination of this trial. All investigation sites approached to take part in this study must count on a staff of registered dietitians to provide the dietary proposed intervention, as well as the physical structure/equipment to allow anthropometric and laboratory assessments.

The study population will include patients with previous diagnosis of MI identified in Hemodynamic Services, outpatient cardiology clinics, or during the period of hospitalization. Outpatients post-MI who volunteered for the trial may be also included. The procedures of randomization, allocation, and follow-up will take place at outpatient clinics of Nutrition at each investigation site.

### Eligibility criteria {10}

Inclusion criteria are as follows: male and female patients over 40 years old with diagnosis of previous MI in the last 2 to 6 months and who have signed an informed consent to participate. Diagnosis of both ST-Elevation MI (STEMI) and non-STEMI defined according to the guidelines [22, 23, 26, 27] must be confirmed at the baseline visit through medical records signed by a cardiologist.

Exclusion criteria are as follows: coronary artery bypass graft (CABG) surgery in the upcoming 16 weeks; acquired immunodeficiency syndrome; chronic inflammatory diseases and chronic use of anti-inflammatory, immunosuppressive, and/or anticonvulsant medications; active cancer (in any stage of current treatment); pregnancy or breastfeeding women; drug and alcohol abuse; physical disabilities that may impair anthropometric assessment; morbid obesity (body mass index [BMI] ≥ 40 kg/m^2^); history of allergy to nut intake; dietary use of nutritional supplements based on dietary fibers, polyunsaturated fatty acids (PUFA) omega-3, phytosterols, multivitamins, and probiotics; and participation in other clinical trials whose intervention may interfere with outcomes. Individuals who regularly eat nuts/oilseeds more than 3 times a week (evaluated by simply asking the consumption during the screening process) should not be included in the study.

To avoid dropout and attrition, we will provide investigator sites with strategies such as the possibility of rescheduling study visits within a 15-day range of both anticipation/delay in appointments, adaptation of financial compensation for transport to study visits according to costs (if that should be the impediment for participation), and motivational talks. If the participant chooses to end participation, investigators will still try to schedule the final study appointment (respecting the intention-to-treat nature of the protocol). When contact with participants is impaired throughout the study (ex. change of contact information), investigators will reach out to the person informed as point of contact during the baseline visit. Dropouts will be considered, hence, only when there is a lack of data in the last study visit, after all attempts of contact with patients are considered as failures to reach out to the patient.

### Who will take informed consent? {26a}

This study complies with national and international good clinical practices (Brazilian RDC 466/12, International Council for Harmonisation/Good Clinical Practices [ICH/GCP], World Health Organization [WHO], and Declaration of Americas). The investigator who approaches eligible participants to the study is responsible for obtaining the written informed consent from all participants (Supplementary Material, Appendix II).

We will financially compensate participants for transportation costs throughout the study, as well as provide them with meals following blood testing in the first and last visit for data collection.

### Additional consent provisions for collection and use of participant data and biological specimens {26b}

This is not applicable. We will not apply additional consent provisions for collection. If this trial subsidizes any further analysis not described in this primary plan, researchers will need to re-get consent from participants.

### Interventions

#### Explanation for the choice of comparators {6b}

DICA Br is a dietary prescription originally designed for secondary cardiovascular prevention guided by nutritional content recommendations as per guidelines and composed by locally available foods in each Brazilian region. Trial participants will be assigned to either of two groups, intervention (Group 1) or control/comparator (Group 2), both provided with dietary counseling based on the recommendations of the DICA Br—which is part of the Brazilian Cardioprotective Nutritional (BALANCE) Program [10–12].

As a strategy to facilitate adherence to the DICA Br, the registered nutritionist counseling prioritizes local and affordable foods and uses heart symbols of different colors a ludic approach to help raise awareness of healthy proportions between food groups [10–12]. The colors (green, yellow, and blue) are those of the Brazilian flag. In summary, foods in the green group are rich in vitamins, minerals, and dietary fibers and have a low energetic density, saturated fatty acids (SFA), and dietary sodium content; the yellow group is mainly composed by foods rich in carbohydrates and vegetal fats; and the blue group comprises animal sources of proteins, with a higher content of dietary sodium, cholesterol, SFA, and energetic density. A fourth group colored red is composed by ultra-processed foods. In allusion to the absence of the color red in the Brazilian flag, foods from this group should be avoided as often as possible.

The registered nutritionists will plan their counseling based on the premises described as follows (Table 1):

**Table 1 Tab1:** Rationale for dietary counseling

Milestones	Registered dietitian activities	
Baseline visit	Daily energy requirements	Pocket formula [10–12] according to the participants’ BMI classification at baseline visit: • 20 kcal/kg for overweight and obese participants (BMI ≥ 25 kg/m^2^, targeting weight loss); • 25 kcal/kg for normal BMI participants (BMI 18.5 to 24.9 kg/m^2^, targeting weight maintenance); • 32 kcal/kg for those with low BMI (BMI < 18.5 kg/m^2^, targeting weight gain).
Baseline visit	Semi-quantitative nutritional counseling	• Dietary counseling to raise awareness of the colored food groups: encourage participants to increase intake of foods in the green group, moderate foods in the yellow group and reduce intake of foods in the blue group in the next 30 days; • The intake of ultra-processed foods (red group) will be strongly discouraged throughout the trial; • Participants will receive an educational material with a brochure to aid food choices (according to color groups), and a recipe book (with tested recipes, adapted to the protocol).
Visits 2, 3, and 4	Quantitative nutritional counseling	• Distribution of daily portions of each food group (colors green, yellow, and blue) into the participants’ routine according to the energy requirements planned at baseline visit; • Use of pre-elaborated menus that balance the amount of green, yellow, and blue food servings (1400 to 2400 kcal) [11] as examples for counseling; • Encourage patients to make their own combinations using the educational materials supplied, so to achieve the energetic goal established at baseline visit;
Visit 5	Qualitative nutritional counseling	• Make final adjustments to counseling and encourage participants to maintain the new healthy patterns acquired after the study’s finished.

*BMI* body mass index

Table 2 shows the lowest caloric menu available (1400 kcal/day) as an example of DICA Br dietary prescription, including dietary composition and the amount of food servings according to color groups [10–12]. Supplementary material shows food group (portions/day) standard harmonization according to energy requirement ranges for DICA Br prescription (Table S1) and an example of a menu/daily food distribution and corresponding number of colored food groups, as a ludic strategy for improving compliance (Chart S2).

**Table 2 Tab2:** Example of dietary prescription (DICA Br and DICA Br - NUTS) including dietary composition and food servings according to DICA Br color groups

	DICA Br composition	DICA Br - NUTS
Total energy, in kcal/day	1400	1600
Carbohydrate, in % TE	57	50
Protein, in % TE	23	23
Total fat, in % TE	20	27
Saturated fatty acids, in % TE	7	9
Monounsaturated fatty acids, in % TE	5	10
Polyunsaturated fatty acids, in % TE	5	7
Dietary cholesterol (mg)	93	94
Dietary fiber (g)	20	22
Green group portions	9	9
Yellow group portions	6	7
Blue group portions	2	2

*% TE* percentage of total energy, *DICA Br DIeta CArdioproterora Brasileira*, *DICA Br - NUTS* DICA Br + 30 g of mixed nuts (10 g of peanuts, 10 g of cashew, and 10 g of Brazil nut)

#### Intervention description {11a}

Group 1 (DICA Br plus 30 g of mixed nuts) participants will be advised to supplement their diet with a daily amount of 30 g of mixed nuts over the intervention period. The research team will provide the participant with individual packages containing a mix of 10 g of toasted cashew nuts, 10 g of raw and peeled peanuts, and 10 g of raw Brazil nuts (all without salt). Each investigator center will receive precision scales with 0.1 to 2000 g accuracy to reassure this procedure. Participants will be advised to eat the nuts plain as a first-line counseling but will be free to use them as culinary ingredients, in case of low adherence (i.e., together with yogurt, mixed with rice or other cereals, etc.), as a secondary line. We will train care providers to counsel such modifications to diet. Participants will be also counseled about adequate storage of the nuts provided.

All nuts will be acquired from local and regional farmers (peanuts: state of Rio Grande do Sul, Southern region of Brazil; cashew nuts: state of Rio Grande do Norte, Northeast region of Brazil; and Brazil nuts: state of Mato Grosso do Sul, Midwestern region of Brazil). Centesimal composition, fatty acid profile, and minerals’ content of the nuts provided in the study, including the methodology used for chemical analysis are described in Supplementary Materials (Table S2 and Appendix I).

Group 2 (only DICA Br) will be advised to follow the recommendations of the DICA Br, and to avoid eating nuts and oilseeds of any type over the intervention period.

Diets will not be isocaloric between intervention and controls, given that while Group 2 will be prescribed a diet according to the energetic goals established only (ex. 1400 kcal/day), Group 1 will be prescribed the same and then added the mixed nuts (ex. 1400 kcal/day + mixed nuts) (Table 2).

All participants will be instructed to maintain and not modify their physical activity levels during the study.

#### Criteria for discontinuing or modifying allocated interventions {11b}

This is an intention-to-treat trial, so we will not exclude data from the database in case of intervention discontinuation and will remain following the participants even without any intervention for the remaining study duration, unless the participant demand not to be followed. We expect a few possible reasons for intervention discontinuation, such as upon request and/or low adherence to intervention; presence of adverse events; presence of any factor that may require specific nutritional therapy other than the provided by the trial; or when the participant develops any of the exclusion criteria. Patients will be prompted to complete the follow-up. Participants who discontinue intervention will be asked to come for the final assessment, for blood sample and data collection.

In case the investigator cannot locate the participant after being randomized, we will train the investigation site to try contact several times. If after exhaustive efforts and the participant’s outcome cannot be determined, we will consider the data as missing (not excluded from the database). Participants may be reallocated among investigation sites when needed (i.e. if a participant moves from one city to another), although data must be analyzed within original randomization site.

#### Strategies to improve adherence to interventions {11c}

Investigators will monitor adherence to intervention through the return of the individual mixed nuts packages (Group 1) and through 24-h food records (both groups) provided at each follow-up visit. In addition, investigators will contact all participants for remembering the visits scheduled and, if necessary, will re-scheduled it according to the participant’s preference. In these calls, the importance of interventions’ adherence will be reinforced.

#### Relevant concomitant care permitted or prohibited during the trial {11d}

The registered nutritionists will encourage participants to avoid in their routines (or to eat them as little as possible) any other amount of nuts and oilseeds other than the mix provided in the study.

#### Ancillary and provisions for post-trial care {30}

This is not applicable. No specific provisions for post-trial care were considered in this trial, due to the characteristic of the intervention, the follow-up period and the outcomes evaluated. All harms and adverse events (AE) will be dealt properly, and if the participants need any health care due to participation in the study, they will be referred to the respective referral services. If the superiority of DICA Br supplemented with mixed nuts is confirmed, participants in the control group will be advised to include these foods in their routine.

#### Outcomes {12}

##### Primary outcome

The primary outcome will consist of LDL-c means (mg/dL) at 16 weeks.

##### Secondary outcomes

Means of other measures of lipid profile (total cholesterol [TC], high-density lipoprotein cholesterol [HDL-c], very low-density lipoprotein cholesterol [VLDL-c], non-HDL cholesterol [NHDL-c], fasting triglycerides [TG], Castelli indexes I and II, and TG/HDL-c ratio) at 16 weeks;Means of glycemic profile variables (fasting glucose [FG], fasting insulin [FI], glycated hemoglobin [HbA1c], and Homeostases Model Assessment-Insulin Resistance [HOMA-IR]) at 16 weeks;Means of anthropometric measures (body weight, BMI, waist circumference, hip circumference, waist to hip ratio, and waist to height ratio) at 16 weeks.

#### Participant timeline {13}

Patients will be invited personally or by telephone to participate in the study. For the individuals who meet the inclusion criteria, a visit will be scheduled with the research team for eligibility confirmation. All individuals will be advised to fast overnight for 12 h before the baseline visit.

After eligibility confirmation and informed consent process, patients will undergo a baseline assessment and a blood sample will be collected. The baseline assessment comprises questionnaires on sociodemographic and lifestyle data (smoking, alcohol intake, and level of physical activity), medical history (including previous diagnosis and drug prescriptions), and dietary patterns. We will also assess anthropometric data (body weight, body height, waist and hip circumferences).

After randomization and once allocation has been completed, the patient will be appropriately advised according to the intervention designated: control diet (DICA Br) or intervention diet (mixed nuts added to DICA Br). Patients will be followed for a period of 4 months (16 weeks), and follow-up visits will be scheduled at 30 days, 60 days, 90 days, and 120 days (final visit), when a new blood sample will be collected. Table 3 summarizes the proposed intervention and study flow.

**Table 3 Tab3:**
[figure not shown]
Study flowchart and summary of data collection

Each investigation site will be responsible for data collection and transcription into both paper and electronic case report form (CRF), at the study website.

#### Sample size {14}

Based on the BALANCE study, the observed correlation between baseline LDL-c and final LDL-c (16 weeks) was 0.6, and the standard deviation was 24. A sample size estimated at 352 participants would guarantee a power of 80% to detect a minimum difference of 6 mg/dL in LDL-c between groups, with two-tailed alpha of 5%. Adding 10% considering possible dropouts, the final sample size will consist of 388 individuals.

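### The sample size of 352 does not follow from the inputs as printed, which give 322 to 324; the gap is conservative at face value and rounding could explain it

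*Protocol article*

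**What the plan says.** Under Sample size {14}, the protocol article takes its inputs from the BALANCE study: "the observed correlation between baseline LDL-c and final LDL-c (16 weeks) was 0.6, and the standard deviation was 24". It then states that "A sample size estimated at 352 participants would guarantee a power of 80% to detect a minimum difference of 6 mg/dL in LDL-c between groups". The test is two-sided at the 5% level. The last step is "Adding 10% considering possible dropouts, the final sample size will consist of 388 individuals".

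Two other sections bear on the calculation. Trial design {8} sets 1:1 allocation. Statistical methods {20a} makes the primary analysis an ANCOVA of 16-week LDL-c with treatment group, site and baseline LDL-c in the model. That analysis explains why a baseline-to-final correlation is quoted. Apart from the 10% for dropouts, which is applied after 352, the article mentions no inflation.

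**The concern.** The sample size section gives every input that the standard ANCOVA formula needs, so a reader should be able to recover 352. The formula returns a total 28 to 30 lower, about 9% of the number required. Rounding up to whole participants, or choosing the t distribution over the normal, moves the total by only 2.

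This is the only sample-size statement in the article, it concerns the single primary outcome, and the enrolment target of 388 is built on it. If the result is null, readers will want to know what the trial could have detected. They cannot tell whether 352 meant 80% or 83% power for 6 mg/dL.

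**Working it through.** **Inputs.** From Sample size {14}: SD 24 (no unit given, taken as mg/dL), correlation r = 0.6, difference 6 mg/dL, power 80%, two-tailed alpha 5%, evaluable N 352, dropout 10%, final N 388. From Trial design {8}: 1:1 allocation. From Statistical methods {20a}: baseline-adjusted ANCOVA. From Trial status: 9 sites.

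**Attempt to reproduce 352.**

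- Residual SD = SD × √(1 − r²) = 24 × √(1 − 0.36) = 24 × 0.8 = 19.2.
- Normal formula: n per arm = 2 × (1.960 + 0.842)² × 19.2² / 6² = 2 × 7.849 × 368.64 / 36 = 160.75. This rounds up to 161 per arm, **322** in total.
- Noncentral t: 162 per arm, **324** in total. The answer is the same whether 3 or 11 degrees of freedom are removed (11 covers group, baseline and the 9 sites).

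The stated 352 is not reproduced.

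**Other readings of the same inputs at two-sided 5% and 80% power.**

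| Reading | SD used | Total N (normal / t) | Power at 352 |
|---|---|---|---|
| ANCOVA | 19.2 | 322 / 324 | 83.2% |
| Change score, SD × √(2(1 − r)) | 21.47 | 402 / 404 | about 74% |
| Unadjusted comparison | 24 | 504 / 506 | about 65% |

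None of them returns 352.

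**What 352 delivers at the printed inputs.** Power by noncentral t is 83.2%. The difference detectable with 80% power is (1.960 + 0.842) × 19.2 × √(4/352) = 5.73 mg/dL.

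**Could rounding explain the gap?** Taking 24 as anything from 23.5 to just under 24.5, and 0.6 as anything from 0.55 to just under 0.65, the t-based ANCOVA total runs as follows:

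- SD 23.5, r 0.649: 282.
- SD 24, r 0.553: 352.
- SD 24.45, r 0.575: residual SD 24.45 × √(1 − 0.3306) = 20.00, total 352, power 80.1%.
- SD 24.49, r 0.55: 368.

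So 352 lies within the range that the printed precision allows.

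**Dropout step (minor).** 352 × 1.10 = 387.2, rounded up to 388. A 10% loss from 388 leaves 388 × 0.9 = 349.2, about 349. Retaining 352 after a 10% loss would take 352/0.9 = 391.1, so 392. Power at 349 is 82.9% at the printed inputs, and about 79.8% if the unrounded inputs are those that give 352. Either way it is about 0.3 points below the power at 352.

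**The case against.** The best defence is rounding. The correlation is given to one decimal and the SD as a whole number, and values that round to exactly those figures can give 352 at 80% power. This stands, and it means that the text does not establish an error in any one input. It does not make the printed calculation reproducible, because the article does not say that rounding occurred and the printed precision allows totals from about 282 to 368.

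A reader might go further and infer that an input or the power is misstated, for instance that the SD was really 25, since SD 25 with r 0.6 also gives 352 by the t distribution. The document does not support that: 25 does not round to the printed 24, and nothing in the article points to it. One-sided 5% with 90% power also gives 352 by the normal formula, but the article states two-tailed 5% and 80%. That several different changes reach the same total shows that the total alone cannot identify the cause. The article also leaves open whether 24 is the baseline or the 16-week SD.

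A second defence is that the mismatch is harmless. At the printed inputs it is conservative, and this stands too.

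On dropout, the text says only that 10% was added, which is what was done. It never claims that 352 remain after a 10% loss, so this is not a second arithmetic error.

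Finally, this is a journal article, and the full protocol may hold the unrounded figures. That would make the correction easy, but the article prints both inputs and result, and as printed they disagree.

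**Conclusion.** The point holds as a failure of reproducibility. With SD 24, r 0.6, a difference of 6 mg/dL, two-tailed 5% and 80% power, the planned ANCOVA needs 322 to 324 evaluable participants, not 352. At those inputs 352 gives about 83% power.

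The calculation assumes that 24 is the SD of 16-week LDL-c in mg/dL, that the two arms share it, and that adjustment for site removes no further variance.

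It would be wrong to conclude that the trial is underpowered. At the printed inputs power stays at 82.9% even after a 10% loss. If the unrounded inputs are those that give 352, it is about 79.8%, which is no meaningful shortfall. What is lost is the reader's ability to tell which of these cases applies.

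**What to change.** Check the original calculation, then restate the paragraph in one of two ways:

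1. If unrounded inputs were used, report the correlation and SD that give 352 at 80% power, and say whether the SD is the baseline or the 16-week value.
2. If SD 24 and r 0.6 are the values used, keep them and state that 352 evaluable participants give about 83% power for 6 mg/dL (equivalently, 80% power for about 5.7 mg/dL).

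In either case, add that 388 enrolled leaves 349 evaluable after a 10% loss, with the matching power: 82.9% at the printed inputs, or about 79.8% if the inputs are those that give 352.

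The cost is rewording one paragraph. The enrolment target stays at 388, of whom 357 had been included by June 2021 according to Trial status.
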